#### Secondary outcomes

The secondary outcomes are:Numerical rating scale [21]: an 11-point patient-reported outcome measure (PROM) with scores ranging from 0 (no pain) to 10 (worst pain)WOMAC [23] pain subscale: a 5-item PROM with total scores ranging from 0 to 20; higher scores indicate worse painWOMAC [23] function subscale: a 17-item PROM with total scores ranging from 0 to 68; lower scores indicate better physical functionWOMAC [23] stiffness subscale: a 2-item PROM with total scores ranging from 0 to 8; higher scores indicate more stiffnessPatient global assessment [24]: a 5-point Likert scale12-item Short Form Health Survey (SF-12) [25] physical dimension: total scores range from 0 to 100; lower scores indicate a worse quality of lifeSF-12 [25] mental dimension: total scores range from 0 to 100; higher scores indicate a better quality of life

For the patient global assessment, participants are asked how their knee symptoms were during the past week. Answers can include “extremely improved,” “slightly improved,” “not changed,” “slightly aggravated,” and “extremely aggravated.”

The NRS, WOMAC, patient global assessment, and SF-12 are measured at 4, 8, 16, and 26 weeks after randomization. The blinding assessment is measured at 4 and 8 weeks after randomization. The credibility and expectancy of participants are measured 5 min after the first acupuncture session [26]. The use of rescue medicine is also recorded throughout the trial.

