#### General analysis principles

All data will be summarized by treatment group. Numbers (percentages) will be used to describe categorical data. Either means (standard deviations) or medians (interquartile ranges) will be used for quantitative data depending on whether the variables are normally distributed. If not otherwise stated, the significance level will be set at 0.05. The Bonferroni method will be used to adjust the significance level for multiple comparisons for the primary outcome. The conclusions will be based on the analysis of the primary outcome, and all secondary outcomes will be analyzed to support the primary analysis. All analyses will be carried out using SAS 9.3 (Cary, NC).

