**Fig. 2 Fig2:**
[figure not shown]
Flow diagram. EA electro-acupuncture, MA manual acupuncture, SA sham acupuncture

The demographic characteristics and clinical outcomes at baseline are those presented in Table 1. Missing data for baseline characteristics will not be imputed. Differences among the treatment groups at baseline will not be statistically tested.

**Table 1 Tab1:** Baseline characteristics

Baseline characteristic	Type	Levels or scale
Gender	Categorical	Male or female
Age	Continuous	Years
Nationality	Categorical	Han or other
Duration of disease	Continuous	Years
Kellgren–Lawrence grade	Categorical	Grade II or III
Body mass index	Continuous	kg/m^2^
Years of education	Categorical	<9, 9–12, or >12
Affected knee	Categorical	Unilateral or bilateral
Previous treatments	Categorical	Injections, medication, physical therapy, acupuncture, exercise, etc.
Concomitant diseases	Categorical	Hypertension, coronary heart disease, diabetes mellitus, hyperlipidemia, etc.
Numerical rating scale	Continuous	Point
WOMAC pain subscale	Continuous	Point
WOMAC function subscale	Continuous	Point
WOMAC stiffness subscale	Continuous	Point
Physical health, SF-12	Continuous	Point
Mental health, SF-12	Continuous	Point

*WOMAC* Western Ontario and McMaster Universities osteoarthritis index, *SF-12* 12-item Short Form Health Survey

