#### Analysis of secondary outcomes

For the NRS score, comparisons among the three groups will be assessed by a mixed-effect model with repeated measurement (MMRM) analysis using the NRS score at all follow-up time points as the dependent variable, treatment as the main factor, and the baseline value as a covariate. We set the model as

*y*_*ij*_ = *α* + *u*_*i*_ + *β*_1_time_*ij*_ + *β*_2_treat_*i*_ + *ε*_*ij*_

where *α* is the overall average and *u*_*i*_ is an unknown random effect represented as a subject-specified effect. *β*_1_ and *β*_2_ are unknown fixed effects represented as time and treatment effects, respectively. The covariance matrix *G* is unstructured, and *u*_*i*_~*N*(0, *G*). The random error *ε*_*ij*_~*N*(0, *R*_*i*_). The MMRM for secondary outcomes will be handled by PROC MIXED (SAS). The estimators of unknown parameters will be calculated using an expectation maximalization algorithm, which we expect will converge for the 480 participants in three groups and a single random intercept. If non-convergence does happen, we will consider correcting the initial value, changing the random effect, or using another analysis method like generalized estimating equations. Also, we will test the estimators or models based on a likelihood test and Bayesian information criterion methods.

The modified MMRM also has the center effect and time × treatment effect and it will be used in the sensitivity analysis. The modified MMRM is as follows:$$ {y}_{ij}=\upalpha +{u}_i+{\upbeta}_1{\mathrm{time}}_{ij}+{\upbeta}_2{\mathrm{treat}}_i+{\upbeta}_3{\mathrm{time}}_{ij}\times {\mathrm{treat}}_i+{\upbeta}_4{\mathrm{center}}_i+{\upvarepsilon}_{ij} $$

where α, u_*i*_, β_1_, β_2_, and ε_*ij*_ are defined as above. β_3_ and β_4_ are unknown fixed effects.

The same approach will be used to analyze the pain, function, and stiffness WOMAC subscales, and SF-12. If normality is violated in the continuous variables, a transformation will be performed before the comparison. A chi-square test will be used for the patient global assessment. These outcomes are shown in Table 2.

**Table 2 Tab2:** Primary and secondary outcomes

Outcomes	EA (*n*)	MA (*n*)	SAb (*n*)	*P* value	Pairwise comparison					
					EA vs. SA		MA vs. SA		EA vs. MA	
					Difference (95% CI)	*P* value	Difference (95% CI)	*P* value	Difference (95% CI)	*P* value
Success rate, no. (%)										
4 weeks	x (xx.x)	x (xx.x)	x (xx.x)	–	xx.x (xx.x- xx.x)	xx.x	xx.x (xx.x- xx.x)	xx.x	–	–

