26 weeks	xx.x (xx.x)	xx.x (xx.x)	xx.x (xx.x)		xx.x (xx.x- xx.x)		xx.x (xx.x- xx.x)		xx.x (xx.x- xx.x)	
Patient global assessment, mean (SD)										
Baseline	xx.x (xx.x)	xx.x (xx.x)	xx.x (xx.x)	xx.x	xx.x (xx.x- xx.x)	xx.x	xx.x (xx.x- xx.x)	xx.x	xx.x (xx.x- xx.x)	xx.x
4 weeks	xx.x (xx.x)	xx.x (xx.x)	xx.x (xx.x)		xx.x (xx.x- xx.x)		xx.x (xx.x- xx.x)		xx.x (xx.x- xx.x)	
8 weeks	xx.x (xx.x)	xx.x (xx.x)	xx.x (xx.x)		xx.x (xx.x- xx.x)		xx.x (xx.x- xx.x)		xx.x (xx.x- xx.x)	
16 weeks	xx.x (xx.x)	xx.x (xx.x)	xx.x (xx.x)		xx.x (xx.x- xx.x)		xx.x (xx.x- xx.x)		xx.x (xx.x- xx.x)	
26 weeks	xx.x (xx.x)	xx.x (xx.x)	xx.x (xx.x)		xx.x (xx.x- xx.x)		xx.x (xx.x- xx.x)		xx.x (xx.x- xx.x)	
SF-12 physical health, mean (SD)										
Baseline	xx.x (xx.x)	xx.x (xx.x)	xx.x (xx.x)	xx.x	xx.x (xx.x- xx.x)	xx.x	xx.x (xx.x- xx.x)	xx.x	xx.x (xx.x- xx.x)	xx.x
4 weeks	xx.x (xx.x)	xx.x (xx.x)	xx.x (xx.x)		xx.x (xx.x- xx.x)		xx.x (xx.x- xx.x)		xx.x (xx.x- xx.x)	
8 weeks	xx.x (xx.x)	xx.x (xx.x)	xx.x (xx.x)		xx.x (xx.x- xx.x)		xx.x (xx.x- xx.x)		xx.x (xx.x- xx.x)	
16 weeks	xx.x (xx.x)	xx.x (xx.x)	xx.x (xx.x)		xx.x (xx.x- xx.x)		xx.x (xx.x- xx.x)		xx.x (xx.x- xx.x)	
26 weeks	xx.x (xx.x)	xx.x (xx.x)	xx.x (xx.x)		xx.x (xx.x- xx.x)		xx.x (xx.x- xx.x)		xx.x (xx.x- xx.x)	
SF-12 mental health, mean (SD)										
Baseline	xx.x (xx.x)	xx.x (xx.x)	xx.x (xx.x)	xx.x	xx.x (xx.x- xx.x)	xx.x	xx.x (xx.x- xx.x)	xx.x	xx.x (xx.x- xx.x)	xx.x
4 weeks	xx.x (xx.x)	xx.x (xx.x)	xx.x (xx.x)		xx.x (xx.x- xx.x)		xx.x (xx.x- xx.x)		xx.x (xx.x- xx.x)	
8 weeks	xx.x (xx.x)	xx.x (xx.x)	xx.x (xx.x)		xx.x (xx.x- xx.x)		xx.x (xx.x- xx.x)		xx.x (xx.x- xx.x)	
16 weeks	xx.x (xx.x)	xx.x (xx.x)	xx.x (xx.x)		xx.x (xx.x- xx.x)		xx.x (xx.x- xx.x)		xx.x (xx.x- xx.x)	
26 weeks	xx.x (xx.x)	xx.x (xx.x)	xx.x (xx.x)		xx.x (xx.x- xx.x)		xx.x (xx.x- xx.x)		xx.x (xx.x- xx.x)	

*EA* electro-acupuncture, *MA* manual acupuncture, *SA* sham acupuncture, *WOMAC* Western Ontario and McMaster Universities Osteoarthritis Index, *SD* standard deviation, *SF-12* 12-item Short Form Health Survey

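### The patient global assessment is an ordered five-level item, but it is tested by a chi-square that ignores the order and tabulated as a mean (SD) that does not match the test, with a Baseline row that has no stated source

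*SAP article*

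**What the plan says.** Under Secondary outcomes, the patient global assessment is a five-point Likert item. On its content the section says: "participants are asked how their knee symptoms were during the past week". The answer options are ordered: "Answers can include “extremely improved,” “slightly improved,” “not changed,” “slightly aggravated,” and “extremely aggravated". On timing: "The NRS, WOMAC, patient global assessment, and SF-12 are measured at 4, 8, 16, and 26 weeks after randomization".

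Under Analysis of secondary outcomes, the whole analysis of this item is one sentence: "A chi-square test will be used for the patient global assessment". No trend or row-mean-score version is named and no categories are combined. The next sentence refers the reader to Table 2.

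In Table 2 the item's block is headed "Patient global assessment, mean (SD", that is, mean with standard deviation. It has rows for baseline and weeks 4, 8, 16 and 26, under pairwise columns for a difference with 95% CI. This is the layout used for the continuous outcomes analysed by the mixed model.

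Two other statements bear on this. General analysis principles says: "Numbers (percentages) will be used to describe categorical data". Descriptive analyses says: "The demographic characteristics and clinical outcomes at baseline are those presented in Table 1". Table 1 lists the NRS, the three WOMAC subscales and both SF-12 scores, but not the patient global assessment.

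**The concern.** The item is treated as unordered categories in the test and as a continuous score in the table, and it is neither.

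- **Test.** A Pearson chi-square on five categories asks whether the distributions differ in any way. It can be significant because of a difference in spread with no net benefit. It can also miss a general move towards improvement that an ordinal test would detect.
- **Table.** A chi-square yields no mean difference and no interval for one. An analyst who fills in Table 2 as drawn will print a P value beside an effect that answers a different question, or will have to choose another method once data are in hand. The article says it exists to prevent such choices.
- **Baseline row.** The answers describe change, and the list of baseline outcomes omits the item. Nothing in the plan says what would go in that row.

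**Working it through.** **1. Plan's own figure (used only to set arm sizes).** The plan gives no sample size or distribution for this item. Its primary calculation reproduces as follows, for 60% vs 40%, two-sided α = 0.025 and 80% power:

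- n = (2.2414·√(2·0.5·0.5) + 0.8416·√(0.6·0.4 + 0.4·0.6))² / 0.2² = (1.585 + 0.583)² / 0.04 ≈ 117.5, so 118 per arm.
- With continuity correction: (117.5/4)·(1 + √(1 + 4/(117.5·0.2)))² ≈ 127.3, so 128 per arm, as stated.
- 128/(1 − 0.2) = 160 per arm, and 3 × 160 = 480, as stated.

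The relevant arm sizes are therefore 128 (after the assumed loss) to 160 (all randomized). The level for secondary outcomes is 0.05.

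**2. Does the planned test use the order?** Illustrative counts, best to worst, 160 per arm: 24/64/48/16/8 vs 40/68/34/12/6.

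- *Chi-square.* Expected counts per arm are 32/66/41/14/7. The statistic is 2·(8²/32 + 2²/66 + 7²/41 + 2²/14 + 1²/7) = 2·(2.000 + 0.061 + 1.195 + 0.286 + 0.143) = 7.37 on 4 df, P = 0.118. Shuffling the five columns leaves P at 0.118.
- *Wilcoxon rank-sum with tie correction.* P = 0.0095 in the true order and 0.69 when shuffled.

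Only the second test uses the order.

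**3. Power.** Assumptions, none of them from the plan: sham distribution 15/40/30/10/5% from best to worst; a common (proportional) odds ratio; two arms of 128 to 160; two-sided α = 0.05. Simulated power, lower figure at 128 and upper at 160 per arm:

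| Odds ratio | Chi-square (4 df) | Rank test |
|---|---|---|
| 1.5 | 25–31% | 41–50% |
| 1.8 | 49–61% | 72–82% |
| 2.0 | 66–78% | 85–93% |
| 2.5 | 90–97% | 98–99% |

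A separate run with 10,000 simulated comparisons per cell agreed to within about 2 percentage points. Two other sham distributions (10/30/40/15/5% and 25/45/20/7/3%) gave much the same: at an odds ratio of 1.8 and 160 per arm, 60–62% vs 81–82%. At an odds ratio of 1 both tests reject about 5% of the time.

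The size is plausible analytically. The noncentrality that gives 80% power on 1 df (7.85) gives about 60% on 4 df.

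**4. A case that goes the other way.** Suppose treatment only moves patients from the second-best to the best category: 30/25/30/10/5% vs 15/40/30/10/5%, at 150 per arm. Chi-square power is then about 81–84% and rank-test power about 25%.

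**5. Consistency of the plan's parts.**

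| Place | Treatment of the item |
|---|---|
| Secondary outcomes | Five ordered answers |
| Analysis of secondary outcomes | Chi-square |
| General analysis principles | Categorical data as n (%) |
| Table 2 | Mean (SD), difference with 95% CI, Baseline row |
| Table 1 (baseline outcomes) | Not listed |

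Nothing elsewhere in the article reconciles the second and third lines with the fourth, or the fourth with the fifth.

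**The case against.** A chi-square on five categories is a valid test of whether distributions differ, and it holds its level. An article may also leave the exact variant to the full SAP. The power loss depends on assumptions. The plan's responder rates correspond to odds ratios of (0.6/0.4)/(0.4/0.6) = 2.25 and (0.7/0.3)/(0.4/0.6) = 3.5. If this item moved as much, which is itself an assumption, the loss would be modest to negligible, and step 4 shows a pattern in which chi-square wins clearly. All of this stands, and it rules out any claim that the rank test is always better. It does not answer the mismatch between test and table, both of which the article states outright.

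Four stronger readings are tempting, and the document does not support them:

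- *The item is measured only from week 4.* The visit list also omits baseline for the NRS, WOMAC and SF-12, which do have baseline values, so it lists follow-up visits and proves nothing about this item. Its absence from Table 1 and the change wording carry the point.
- *The item cannot be answered at baseline.* The question refers to the past week and gives no reference point for the change. A baseline answer is unexplained, not impossible.
- *Baseline differences will be tested.* P-value cells on the Baseline rows may be merged cells broken in extraction, and the text says that baseline differences will not be tested.
- *The trial's conclusion is at risk.* General analysis principles rests conclusions on the primary outcome and treats secondary outcomes as support.

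**Conclusion.** The point holds as a should-fix matter for one secondary outcome. The document itself shows that the planned test ignores the item's order, that Table 2's means, mean differences and intervals do not correspond to that test and depart from the n (%) rule, and that the Baseline row has no stated source.

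The size of the power cost is conditional. Under the assumed sham distribution and a shift of the whole scale, it is roughly 15 to 25 percentage points at odds ratios from 1.5 to 2.0 and under 10 points at 2.5. It reverses if only adjacent categories exchange patients. Type I error and the primary conclusion are not affected.

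**What to change.** - **Analysis.** Name one ordinal analysis for each follow-up week, for example a proportional-odds model or a Wilcoxon/row-mean-score test. Stratifying by centre, the randomization factor, is optional.
- **Table 2.** Replace mean (SD) with n (%) per category, and give the effect measure that belongs to the chosen analysis with its 95% CI (for a proportional-odds model, the common odds ratio).
- **Baseline row.** Delete it, or state where the baseline value comes from and what the change refers to.

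The cost is a few words in the SAP and an edit to the table shell, with no new data. The downside is some reliance on a common-shift assumption. Showing the category counts lets a reader see any departure from it.

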## Methods/design

### Study design

This three-arm randomized sham-controlled trial has been approved by the ethics committees at each of the nine participating hospitals. Eligible KOA participants, diagnosed according to the American College of Rheumatology criteria [19], are randomly assigned (1:1:1) to receive 24 sessions of EA, MA, or SA over 8 weeks. The block randomization, with block sizes of 6 and 9, is stratified by study center and is performed via a web-based randomization system. Superficial insertion at non-acupoints with no electric current will be used for the SA group, which is one of the most commonly used approaches for administering sham treatments in acupuncture trials. The nature of acupuncture means that acupuncturists are not blinded to treatment allocation; however, patients, outcome assessors, and statisticians will remain masked. Informed consent will be obtained from each participant before randomization. The trial has been registered with ClinicalTrials.gov (NCT03366363).

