### Sample size

Based on the results of our previous trial [16], the response rates for the EA, MA, and SA groups were assumed to be 70%, 60%, and 40%, respectively. With a two-sided significance level of 2.5% and power of 80%, 128 participants in each group will be required to detect a difference as small as 20% between each acupuncture group and the control group. The two-sided significance level of 2.5% is a Bonferroni-adjusted alpha level as per the two predefined primary comparisons: EA vs. SA and MA vs. SA. With an estimated loss-to-follow-up rate of 20%, 480 participants will be recruited in total.

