#### Analysis of the primary outcome

In the analysis of the primary outcome, the response rates of the three groups at 8 weeks will be calculated and the *Z*-test for comparisons of proportions will be used with the full analysis set. Any missing data at 8 weeks will be imputed using the baseline value. There will be two comparisons. The first comparison is that between the EA group and the SA group. The second is that between the MA group and the SA group. The significance level will be adjusted at 0.025 for multiple comparisons using the Bonferroni method.

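### Table 2 pairs the two primary tests, run at 0.025, with 95% confidence intervals that are not marked as unadjusted

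*SAP article*

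**What the plan says.** The plan is consistent about the level of the primary tests. The Sample size section says: "The two-sided significance level of 2.5% is a Bonferroni-adjusted alpha level as per the two predefined primary comparisons". The section on the analysis of the primary outcome repeats it for EA vs SA and MA vs SA at 8 weeks: "The significance level will be adjusted at 0.025 for multiple comparisons using the Bonferroni method". The general analysis principles confine the Bonferroni adjustment to the primary outcome, use 0.05 elsewhere by default, and rest the conclusions on the primary analysis.

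Table 2 is the shell for reporting primary and secondary outcomes. Each pairwise comparison has a column headed "Difference (95% CI" and a P value column beside it. One header serves every row, including the 8-week success-rate row, which is the primary outcome. No footnote or sentence gives another confidence level for that row, or says that the intervals are unadjusted for the two comparisons.

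**The concern.** A two-sided test at 0.025 corresponds to a 97.5% interval. In the primary row, test and interval therefore work at different levels. Whenever P falls between 0.025 and 0.05, the row shows an interval that excludes zero next to a comparison that failed its pre-specified test.

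What is at stake is how the main result is read. Many readers look first at the interval, and nothing in the table tells them that it carries no allowance for the second comparison. The article states that it aims to reduce reporting bias, and an unlabelled interval that can look positive beside a failed test works against that aim.

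**Working it through.** **Inputs from the Sample size and Study design sections.** Assumed rates: "the response rates for the EA, MA, and SA groups were assumed to be 70%, 60%, and 40%, respectively". Design: "With a two-sided significance level of 2.5% and power of 80%, 128 participants in each group will be required". Recruitment: "With an estimated loss-to-follow-up rate of 20%, 480 participants will be recruited in total". Allocation is 1:1:1.

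**Step 1. Reproduce the stated sample size.** For 60% vs 40% at two-sided 0.025 and 80% power:

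n = [z(0.9875)·√(2·0.5·0.5) + z(0.80)·√(0.6·0.4 + 0.4·0.6)]² / 0.20²
= [2.2414·0.7071 + 0.8416·0.6928]² / 0.04 = 117.5

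With continuity correction, (n/4)·[1 + √(1 + 4/(n·0.20))]² = 127.3, which rounds up to 128, as stated. Then 128/0.80 = 160 per arm, and 3 × 160 = 480. The same formula at 0.05 gives 107, so the stated number does rest on 0.025.

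**Step 2. Compare the interval multipliers.** A 95% interval uses 1.960 and a 97.5% interval uses 2.241. The ratio is 2.241/1.960 = 1.14, so the matching interval is 14% wider.

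**Step 3. One data set that shows the conflict.** Take 83/160 vs 64/160 (51.9% vs 40.0%).
- Difference: 19/160 = 11.9 points.
- Pooled Z-test: pooled rate 147/320 = 0.4594; standard error √(0.4594·0.5406·2/160) = 0.0557; Z = 0.1188/0.0557 = 2.13; P = 0.033. The test fails at 0.025.
- Interval with unpooled standard error √[(0.5188·0.4813 + 0.4·0.6)/160] = 0.0553: the 95% interval is 1.0 to 22.7 points and excludes zero; the 97.5% interval is -0.5 to 24.3 points and includes it.

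**Step 4. How often this can happen.** The probability that the two-sided pooled Z-test P value lies between 0.025 and 0.05, per comparison, was found by exact binomial enumeration:

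| True rates | 160 per arm | 128 per arm |
|---|---|---|
| 40% vs 40% | 2.2% | 2.3% |
| 50% vs 40% | 9.8% | 9.1% |
| 55% vs 40% | 9.9% | 9.5% |
| 60% vs 40% (planned MA vs SA) | 4.2% | 5.2% |
| 70% vs 40% (planned EA vs SA) | 0.03% | 0.2% |

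The plan imputes missing week-8 data with the baseline value, which makes such a participant a non-responder. If the full 20% loss were handled this way, the planned rates would shrink to 0.8 × 60% = 48%, 0.8 × 70% = 56% and 0.8 × 40% = 32%. At 160 per arm the probability is then 7.1% for 48% vs 32% and 0.7% for 56% vs 32%. This is an upper-end illustration, because participants with no post-baseline measurement leave the modified full analysis set.

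**Step 5. Reading both intervals as tests.** With 40% in all three arms, 160 per arm and a shared SA group, the chance of at least one false positive is the sum over SA counts c of f(c)·[1 − A(c)²]. Here f(c) is the binomial probability of c, and A(c) is the chance that one comparison is not significant given c. The result is 8.7% with 0.05 for each comparison and 4.8% with 0.025 for each (upper bounds 10% and 5%).

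**Step 6. Does 97.5% alone remove the conflict?** Not entirely. With a pooled Z-test and an unpooled interval at 160 per arm, a 97.5% interval still excludes zero beside a failed test with probability 1.4% at 60% vs 40% and 2.5% at 55% vs 40%. The plan does not say which standard error either uses, so this pairing is an assumption.

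**The case against.** The strongest defence is that the inference itself contains no error. The decision rule is stated the same way throughout, conclusions rest on the Z-test at 0.025, and no section makes the interval a criterion of success. Table 2 prints a P value beside each interval, so a reader can apply 0.025 directly. A 95% interval labelled as such is a valid estimate for a single comparison. The plan adjusts the significance level and never promises joint coverage of the two differences. All of this stands.

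A reader might infer that the mismatch inflates the trial's type I error to 8.7%. The document does not support that: the figure describes someone who sets aside the stated test and uses the intervals instead, which is not the plan's rule. A reader might also infer that a conflict is likely if the planning assumptions hold. It is not: the chance is 4.2% for the planned MA contrast and 0.03% for the planned EA contrast at 160 per arm. The figures near 10% need true differences of 10 to 15 points, below the 20 points that the trial is sized to detect.

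The defence leaves one gap. The article prints the results table and fixes the confidence level in it, so this is not detail left to a fuller document, and nothing tells the reader that the two primary intervals work at a different level from the tests beside them.

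**Conclusion.** The mismatch is real and confined to two cells: the week-8 response-rate differences for EA vs SA and MA vs SA. It affects reporting and interpretation. The pre-specified test, its error rate and the sample size are untouched. In the other rows, 95% intervals agree with the default level of 0.05.

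The size depends on the true effect: negligible for the planned EA contrast, a few per cent for the planned MA contrast or under no difference, and about one in ten for intermediate effects. These figures assume a pooled Z-test without continuity correction and 160 analysed per arm; at 128 per arm they change little. The priority is moderate: it concerns the trial's main result and is cheap to repair, but it does not endanger the formal conclusion.

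**What to change.** In Table 2, report 97.5% intervals for the two week-8 response-rate differences and label them so. Name the interval method and match it to the Z-test, so that interval and test agree at the boundary. Add one sentence saying that the primary conclusion follows P < 0.025 for each comparison, and that the 95% intervals in all other rows are unadjusted for multiplicity.

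A weaker but acceptable alternative is to keep 95% intervals in the primary row with a footnote saying that they are unadjusted and that P < 0.025 decides.

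The cost is a table label and one sentence. The two intervals become about 14% wider. No data, test or sample size changes.
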